#### Sample size calculation

The sample size calculation is based on the superiority trial hypothesis test and is driven by the expected improvement in metabolic equivalents (METs). Referring to data from preliminary clinical trials (27, 28), we assume that the minimum difference in improvements of METs between groups over a 12-week treatment period would be 1.38, and the combined standard deviation would be 1.56. According to relevant literature and experts' advice, the superiority margin is 0.42. Considering a 20% dropout rate and referring to calculation results from PASS 15.0 software, 144 participants would achieve 90% power and a one-sided 2.5% significance level. For the convenience of randomization, a sample size of 150 is identified.

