#### The primary and secondary outcomes

The primary outcome is the improvement of METs in CPET. METs are an important indicator for evaluating aerobic metabolism and cardiorespiratory fitness. 1 MET equals 3.5 ml O_2_/kg/min. An increase in exercise capacity manifested by MET can bring great survival benefits. Small increases in cardiorespiratory fitness (e.g., 1–2 METs) are associated with considerably (10% to 30%) lower adverse cardiovascular event rates (30). CPET will be performed at baseline and the end of the 12-week treatment period. Changes from the baseline will be compared between groups.

The secondary outcomes are as follows:

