#### Data analysis

The statistical analysis will be conducted using SAS software (version 9.4). According to the “intention to treat” principle, the full analysis set (FAS) is defined as all participants randomized in the trial, with at least one experimental drug treatment history and at least one therapeutic session visit. Per protocol set (PPS), exclude participants found to be ineligible after randomization or deviate from the intervention or follow-up protocols. The safety analysis set will include all randomized patients who have completed at least one study visit. Finally, we will draw conclusions according to the analysis results of FAS. PPS will be used for sensitivity analysis.

For quantitative data meeting normal distribution, means with standard deviations will be calculated, otherwise, medians with quartile ranges will be shown. While for qualitative data, frequencies and percentages will be described. Comparison between groups will be performed by independent t-tests, or Wilcoxon rank-sum test for quantitative data, and the chi-square test or Fisher's exact test for qualitative data. Subgroup analyses will be conducted on those with PHQ-9 or GAD-7 scores ≥ 5 or < 5. Confounding factors that are difficult to control and unbalanced between groups will be used as covariates to analyze covariance to eliminate their influence on efficacy evaluation. *P* < 0.05 will be considered statistically significant. The last observation carried forward is supposed to estimate missing outcome data. Regarding safety, the number of AEs and SAEs will be categorized, and the incidence rate will be calculated. The data monitoring committee is not formally established because the trial has a short duration and known minimal risks. However, some form of data monitoring will undoubtedly be conducted by inspectors appointed by PI to ensure the accuracy and integrity of data.

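### For METs, LOCF is baseline carried forward: if the planned 20% dropout enters the FAS, power against the 0.42 margin is about 76–82%, not 90%, and unequal dropout can bias the effect either way

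*Protocol article*

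**What the plan says.** The primary outcome is the improvement in METs. The section on primary and secondary outcomes fixes the measurement times, "CPET will be performed at baseline and the end of the 12-week treatment period", and the scale, "Changes from the baseline will be compared between groups". Table 2 agrees: CPET is marked at screening and week 12, with none at week 4 and no early-termination test.

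The Data analysis section states one rule for missing outcomes and makes no exception for the primary endpoint: "The last observation carried forward is supposed to estimate missing outcome data". It adds: "Finally, we will draw conclusions according to the analysis results of FAS". Entry to the FAS requires randomisation "with at least one experimental drug treatment history and at least one therapeutic session visit", which a week-4 visit satisfies.

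The Sample size calculation section reads "we assume that the minimum difference in improvements of METs between groups over a 12-week treatment period would be 1.38". It takes the pooled SD as 1.56. With a superiority margin of 0.42 and 20% dropout, it concludes that "144 participants would achieve 90% power and a one-sided 2.5% significance level". The total is then rounded up to 150.

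The section on withdrawal, dropout and removal asks sites to contact lost or withdrawn patients by telephone or letter, to record outcomes at discontinuation, and to try to obtain later evaluations. It also lists grounds on which a patient may be removed, and removed cases are left out of the efficacy analysis.

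**The concern.** With a single post-baseline measurement, the last observation available to carry forward is the baseline value. For METs, LOCF therefore means an imputed change of zero for every FAS patient without a week-12 CPET. A telephone call or letter cannot supply a MET value.

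The sample size and the analysis thus handle the same patients differently: the first discards them, the second keeps them as zeros. Zeros pull the difference toward no effect while the margin stays at 0.42, and they enter the test as if observed. If patients in both arms tend to improve, more zeros in one arm than the other also move the estimate for reasons unrelated to the drug.

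The rule is written into the protocol, so this is not a detail left to a statistical analysis plan that is not shown.

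A lesser issue concerns the scales measured at weeks 24 and 36. Treatment ends at week 12, so LOCF can carry an on-treatment score into an off-treatment visit and may misstate how long an effect lasts.

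**Working it through.** **Inputs from the protocol article.** Difference 1.38, SD 1.56, margin 0.42, one-sided alpha 2.5%, power 90%, dropout 20%, 1:1 allocation, N = 144 raised to 150.

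**Inputs assumed.** The mean placebo change (muC) is not given, so it is varied from 0 to 1.0 METs, with muT = muC + 1.38. Arm-specific dropout is not given either, so the unequal patterns below are illustrations. Dropouts are taken to have the same underlying distribution of change as completers.

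**1. The plan's own figure.** The excess over the margin is 1.38 − 0.42 = 0.96. A noncentral t calculation needs 57 per arm (power 90.3%). Then 57/0.8 = 71.25, rounded up to 72 per arm, or 144 in total. This is an exact match, and it treats dropouts as lost. With 150 randomised and 20% lost, 60 per arm remain and power is 91.7%.

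**2. The same 20% kept as zeros.** With a fraction d imputed:
- arm mean = (1 − d)·mu
- arm variance = (1 − d)·SD² + d(1 − d)·mu²
- power = Phi((difference − 0.42)/SE − 1.96)

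The expected difference is 0.8 × 1.38 = 1.104, and its excess over the margin is 0.684 instead of 0.96.

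Example with muC = 0 and 75 per arm:
- QTG variance: 0.8 × 2.4336 + 0.16 × 1.9044 = 2.2516
- placebo variance: 0.8 × 2.4336 = 1.9469
- SE = √(4.1985/75) = 0.2366
- power = Phi(0.684/0.2366 − 1.96) = Phi(0.931) = 82.4%

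| Placebo change (METs) | Power, N = 144 | Power, N = 150 |
|---|---|---|
| 0 | 80.9% | 82.4% |
| 0.5 | 78.1% | 79.7% |
| 1.0 | 74.1% | 75.8% |

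Simulated t-tests (40,000 runs) at N = 150 give 82.4% and 79.8% for placebo changes of 0 and 0.5. Restoring 90% under this rule would take about 95 to 102 per arm (placebo change 0 to 0.5).

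**3. What the shortfall depends on (N = 150).**
- If half the dropouts leave before week 4 and are outside the FAS, 67.5 per arm remain with 0.1/0.9 = 11.1% imputed. The difference is 1.227 and power is 86.4–87.7% (placebo change 0.5 to 0).
- Power stays at 90% or above if no more than about 11–12% are imputed (placebo change 0.5 to 0).
- Tested against zero instead of 0.42, power with 20% imputed is 99.0–99.7% (placebo change 1.0 to 0).

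**4. Bias.** Relative to the full effect, the bias is −(dT·muT − dC·muC).

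| Dropout QTG / placebo | Placebo change (METs) | Expected difference (true 1.38) |
|---|---|---|
| 20% / 20% | any | 1.104 |
| 30% / 10% | 0.5 | 0.866 |
| 10% / 30% | 0.5 | 1.342 |
| 10% / 30% | 1.0 | 1.442 |
| 0% / 20% | 0.5 | 1.480 |
| 0% / 20% | 0 | 1.380 |

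**5. Type I error (75 per arm).** If both arms truly improve by 0.5 METs and dropout is 10% on QTG and 30% on placebo, the imputed difference is 0.9 × 0.5 − 0.7 × 0.5 = +0.10. The one-sided error against zero is 6.4% instead of 2.5%. With a placebo change of 0.5 and a true difference equal to the margin, the imputed difference is 0.9 × 0.92 − 0.7 × 0.5 = 0.478, and the error against the margin is 4.4%. Reversing the dropout pattern gives −0.10 and an error of 0.8% against zero.

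**The case against.** The strongest reply is that about 80% is one reading of the plan, not its fixed consequence. Patients lost before the week-4 visit do not enter the FAS. Patients who used less than 80% of the drug may be removed, and many early dropouts would qualify; on that reading they are excluded, as the sample size assumed. The Data analysis section names t-tests or Wilcoxon tests at P < 0.05 and no margin, and against zero there is no shortfall. With equal dropout the zeros work against QTG, and a spurious 0.10 METs is well below 0.42. Finally, missing at random supposes that dropouts fared like comparable completers, which is not self-evident for people who stopped treatment.

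Most of this limits the size of the point without removing it. The removal rule and the FAS definition pull in different directions, which itself needs settling. The false-positive risk does need both unequal dropout and improvement on placebo. The doubt about missing at random is fair and is the reason for a sensitivity analysis.

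A reader might also infer three stronger things that the protocol article does not support:
- That bias appears exactly when dropout differs by arm. It is present with equal dropout, and it can be absent with unequal dropout (only placebo patients drop out and their mean change is zero).
- That every case with incomplete data is removed. The wording is that patients may be removed, and the ground is incomplete data together with no evaluable records after randomisation.
- That durability on the scales is overstated. This would require scores to worsen off treatment in the patients who are missing, and the article says neither.

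**Conclusion.** The point stands in conditional form. On the stated CPET schedule, LOCF fixes the MET change at zero for every FAS patient without a week-12 test, and the stated 90% was calculated without that rule. If all of the planned 20% enter the FAS this way and the 0.42 margin is tested, the expected difference is 1.10 and power with 150 patients is about 76–82%. This assumes a placebo change of 1.0 down to 0 METs and dropouts who would have changed as completers did.

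It would be too strong to say that the trial simply lacks 90% power. The figure is right if dropouts are excluded. It is about 86–88% if half of them leave before week 4, and there is no shortfall if the test is against zero. Equal dropout shrinks the assumed effect; unequal dropout can move it either way, so LOCF cannot be defended as reliably conservative. For the scales, LOCF may misstate durability, in a direction the document does not determine.

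**What to change.** - **Primary endpoint.** Replace LOCF with an analysis valid under missing at random. One example is ANCOVA of week-12 METs on baseline METs and centre, with multiple imputation by arm that also uses the week-4 scale scores.
- **Sensitivity.** Keep baseline carried forward, or a reference-based or delta-adjusted imputation, as a sensitivity analysis.
- **Repeated scales.** Use a mixed model for repeated measures on the observed SAQ, SF-12, PHQ-9 and GAD-7 scores.
- **If LOCF is kept.** Restate power as a range with its assumptions (about 76–82% with 150 patients if 20% are imputed).
- **In either case.** Reconcile the removal rule with the FAS definition, so that it is clear which dropouts are analysed.

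The cost is rewording, some extra programming, and reliance on a missing-at-random assumption that the sensitivity analysis tests. No patients or visits are added. The change should be made before unblinding, because a later change to the primary imputation rule would look data-driven.

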#### Quality control

Inspectors assigned by the PI will visit branch centers three times a year during the trial to monitor the conduct of the clinical trial. The PI will arrange several clinical research coordinators to solve problems generated during the trial and strengthen contacts between trial centers. Before trial initiation, physicians, investigators, outcome assessors, and statisticians will be trained uniformly regarding the study objective, study protocol, informed consent, and relevant standard operating procedure. An independent clinical event committee represented by academician [name] will be set to distinguish the major adverse cardiovascular events (MACEs).

Measures taken to reduce bias: All operators in these four research centers will receive training correlated with the standard operation procedures, cautions, and termination indicators of CPET and finally undergo a consistency evaluation. A symptom-restricted scheme with a ramp power escalation pattern will be adopted. The work rate increasing rate of CPET will be calculated according to the participant's age, sex, height, and weight (31). For the same subject, the work rate increasing rate will stay the same before and after the trial. In addition, CPET outcomes are easily influenced by the examination time and subjects' physical and emotional status. We demand that the examination time should be kept as consistent as possible for the same person. Participants are required not to perform high-intensity exercise 1 day before testing. Daily exercise intensity can also incur bias to METs, so participants are asked to keep similar daily exercise habits to before. Patients will be provided a diary card to record medication status and uncomfortable symptoms. Two Chinese medicine experts will blindly evaluate the TCM syndrome diagnosis of every participant.

Plans to promote participant retention and complete follow-up. Send text messages or give a ring to patients before the follow-up visit, reminding them of the upcoming data collection.

## Discussion

Atherosclerotic cardiovascular diseases are the leading cause of global mortality and a major contributor to disability. Continuing rising healthcare costs have caused substantial financial burdens to societies (32). Implementing effective prevention and treatment strategies is vital to reduce morbidity and mortality in CHD. The popularization of CR has shed light on the tough problem (33). Combined treatment of traditional Chinese medicine and Western medicine has been considered an effective CR mode. This trial is designed as a multicenter, randomized, double-blind, placebo-controlled study aiming to evaluate the effect of QTG on exercise tolerance, angina pectoris, anxiety/depressive symptoms, and prognosis in patients with CHD.

A retrospective cohort study of community-based exercise rehabilitation indicated that higher baseline submaximal cardiorespiratory fitness was associated with a reduced risk of all-cause mortality over 14 years in adults with CHD, and improved fitness was linked with significant risk reduction for the least fit (34). A study examining the prognostic value of exercise capacity in patients with nonvascularized and revascularized coronary artery disease manifested that exercise capacity was a strong predictor of mortality, MI, and downstream revascularizations. Furthermore, patients with similar exercise capacities had an equivalent mortality risk, irrespective of baseline revascularization status (35). CPET is the optimal instrument to measure patients' cardiopulmonary endurance noninvasively. To our knowledge, evidence regarding evaluating the effect of botanical drug products on the cardiopulmonary fitness of CHD patients is rare. So this trial has great significance in enriching alternative treatment therapies for CHD. The design and implementation of the study protocol completely conform to relevant international statements. We also take a series of measures to control quality throughout the study.

There also exist some limitations to this study. First, a 12-week therapeutic session and a 24-week follow-up visit are set. The relatively short duration of follow-up may be difficult to observe the occurrence of MACEs. However, previous studies have demonstrated that higher exercise tolerance is a good surrogate marker for long-term prognosis (13, 35, 36), so this trial may infer some guidance significance in Chinese herbal medicine improving the prognosis of SCAD. Second, the manufacturers of CPET equipment at four centers are not in full accordance with each other, so this may infer some measurement bias. While we will conduct unified training for outcome assessors concerning the operation scheme of CPET before trial initiation.

## Conclusion

This randomized, placebo-controlled trial evaluates the efficacy and safety of Qixue Tongzhi Granule in improving the exercise capacity and long-term prognosis of patients with SCAD, which may create a new situation for promoting the application of traditional Chinese medicine in cardiac rehabilitation.
